
**Table 1 Tab1:**
[figure not shown]
Schedule of enrolment, interventions, and assessments for iSupport intervention study.

**Fig. 1 Fig1:**
[figure not shown]
Participant selection flowchart

Eligible participants will be automatically included in a database to be randomized and assigned to either the intervention or control arm. Included participants will be prompted on the screen to continue filling in the questionnaire in order to complete the baseline assessment (*t*_0_). This means that a single questionnaire is programmed into the study platform and organized in a hierarchical and conditional manner: for participants not meeting the inclusion criteria, the system will terminate the questionnaire while for included participants, the system will display all study instruments for the baseline assessment. Of note some questionnaire items are used both to verify inclusion criteria and to measure covariates (e.g. caregiving duration) or outcomes (caregiver burden; symptoms of depression and anxiety). With the list of participants consecutively included in the database, the researcher applies the randomization key to allocate the IC to the intervention or control group (see section Randomization and blinding). In accordance to the allocated group, the participant receives, by email, either a user code/password (2) to access the iSupport platform or a link to download the e-book.

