### Randomization and blinding

Eligible participants are randomly assigned to the intervention or to the control arm by using a permuted block randomization strategy to maintain reasonably good balance among groups. Blocks of four with equal number of As (intervention) and Bs (control) will be used, with the order of interventions within the block being randomly permuted (1 = AABB, 2 = ABAB, 3 = ABBA, 4 = BAAB, 5 = BABA, 6 = BBAA). Baseline characteristics of individuals randomized to each condition will be compared to verify if the randomization was successful. Health professionals referring the participants to the study platform are not aware of the randomization sequence, and even if they were, they could not control the participants’ allocation as they could not predict the sequence status at the time of the participants’ access to the study platform. Similarly, the researcher assigning the participants to each arm has no control over the order of enrolment (i.e. over who will access the online platform and when), and differs from the researcher performing the statistical analysis at a subsequent stage. The data analyst will be blinded to the intervention assigned to the participants. The study is single-blinded: participants are not unaware of the intervention received as they are active parts of the intervention. Data collection at baseline and outcome assessments are carried out in a computerized manner via study platform and resorting to self-administered instruments, thus the researcher has no influence over the measurements.

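### The researcher who ties each participant to an arm applies the randomisation key to the list of included participants, and the stated safeguard does not cover that step

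*Protocol article*

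**What the plan says.** The route from login to assignment is set out after Fig. 1, in the part of the protocol article on sampling and recruitment.

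- **Entry is automatic.** "Eligible participants will be automatically included in a database to be randomized and assigned to either the intervention or control arm". Those who do not qualify are stopped by the software: "for participants not meeting the inclusion criteria, the system will terminate the questionnaire".
- **Assignment is made by a person.** "With the list of participants consecutively included in the database, the researcher applies the randomization key to allocate the IC to the intervention or control". The participant is then emailed either the iSupport access code or the e-book link.

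The section on randomization and blinding adds the rest.

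- **Sequence.** "Blocks of four with equal number of As (intervention) and Bs (control) will be used". The article lists the six possible orders and says that chance decides which one each block takes.
- **Referrers.** "Health professionals referring the participants to the study platform are not aware of the randomization sequence", and they could not predict where it stands when a participant logs on.
- **Assigning researcher.** The protection given is that "the researcher assigning the participants to each arm has no control over the order of enrolment". This person is also not the analyst, and the analyst is blinded.
- **Participants.** They know which intervention they receive, and they complete all outcome measures themselves online.

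**The concern.** Random assignment prevents selection bias only if whoever links a participant to an arm cannot act on knowledge of the arm. Here the linking is done by someone who applies the key to a list of people already waiting for assignment. The safeguard stated for that person concerns an earlier event, namely who enters the list and in what order. It says nothing about whether the list is then followed.

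The other protections are thin. Participants are unblinded and all outcomes are self-reported, so a sound assignment step carries much of the protection against bias. The statistical analysis section justifies the intention-to-treat analysis by the benefits of randomisation, including freedom from selection bias. That holds only if the key was followed. The background section itself lists selection bias among the weaknesses of earlier studies of such interventions.

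**Working it through.** **1. Steps and protections side by side**

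| Step | Who acts | Protection described | Does it cover the step? |
|---|---|---|---|
| Referral | Health professional | Unaware of the sequence and cannot predict it | Yes |
| Timing of login | Participant | Nobody on the team controls it | Yes |
| Eligibility and entry to the list | Platform | Automatic; ineligible users are stopped | Yes |
| Linking a listed participant to an arm | Researcher with the key | No control over who entered or when | No |
| Analysis | A different researcher | Blinded to arm | Yes, but after assignment |

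The fourth row is the gap. A person can have no influence over the order of a list and still depart from it when applying the key. The article describes no lock on the list, no holding back of the key until an ID is fixed, and no comparison of issued assignments with the key. The planned baseline comparison sets one group against the other. It does not check assignments against the sequence.

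**2. Number of assignments affected**

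The sample size section gives 16 ÷ 0.25 = 64 per group, and 64 × 1.43 = 91.5, so 92 per group. This reproduces, and the total is 2 × 92 = 184. All 184 assignments pass through this step. In blocks of four that is 184 ÷ 4 = 46 blocks.

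**3. Whether block size matters**

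For someone who holds the whole key, every assignment is known in advance whatever the block size. Block size matters only to an observer who sees all earlier assignments in order but not the key. For that observer, with fixed blocks of four:

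- The fourth place is always certain. The third is certain when the first two are alike, which holds in 2 of 6 orders. The share certain is 1/4 + (1/4 × 1/3) = 1/3, or 184 × 1/3 ≈ 61 assignments.
- The best guess is right with probability 1/2, 2/3, 2/3 and 1 at the four places. The mean is (17/6) ÷ 4 = 17/24 = 70.8%.
- With sizes varied at random among 4, 6 and 8 (an assumed set), simulation of lists of 184, guessing from the running imbalance, gives about 68.0%.

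The gain is about 3 percentage points, and it concerns an observer the article does not describe. Changing the block size would not close the gap in the fourth row.

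**The case against.** The strongest reply is that concealment mainly protects the decision to enrol, and that decision is well protected here. Referrers do not know the sequence, participants log on when they choose, and software decides eligibility and entry before any arm is assigned. No one who knows the next arm decides who comes in. This stands. What remains is the narrower risk of a departure from the key after inclusion.

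A reader might go further and infer that allocation in this trial is simply not concealed, or that the published blocks of four make the next assignment known. The article does not support either reading. Concealment from referrers is stated. Only the six possible orders are printed, not the realised sequence, so the next arm is known through the key and not through the block size.

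Some details should not be read in either. The list holds participants already found eligible, not everyone screened. The article does not say that the assigning researcher sees burden or anxiety and depression scores, and it gives that person no power to exclude anyone.

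Finally, this is a condensed article. The full protocol, Fig. 1 and the SPIRIT checklist are not visible, and any of them might describe a lock or an independent key holder. Silence on those details alone would be no finding. But the article does describe the assignment procedure and offers a specific defence of it, and that defence does not reach the step in question.

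**Conclusion.** The point holds in limited form. As described, the sequence is not concealed from the researcher who ties each participant to an arm, and the stated safeguard would neither prevent nor detect reordering, skipping or swapping before the email is sent. This applies to all 184 planned assignments.

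The conclusion assumes that applying the key means having access to it ahead of the assignment, and that no further control exists in documents not shown. The size of any bias in ZBI points cannot be derived: it would depend on how often the key was departed from and on what the researcher could see, and the article gives neither. There is no ground for suspecting misconduct. The case for change is that a better procedure is available at little cost, not that the trial is shown to be biased.

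**What to change.** Load the sequence into the study platform, hidden from the research team. Once a participant's entry is locked, have the platform release one irrevocable, time-stamped assignment in database order and trigger the access email.

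If the platform cannot do this, have an existing colleague who does not handle participants hold the key and release each arm only after the participant ID is locked.

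Amend the randomization and blinding section to say who generates and holds the sequence, and that it is concealed from whoever handles assignment as well as from referrers.

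The cost is a small programming change, or one colleague's time, and one revised paragraph. No extra participants or visits are needed. Randomly varying block sizes may be added if convenient, but would not replace this change.

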### Randomization and blinding

Eligible participants are randomly assigned to the intervention or to the control arm by using a permuted block randomization strategy to maintain reasonably good balance among groups. Blocks of four with equal number of As (intervention) and Bs (control) will be used, with the order of interventions within the block being randomly permuted (1 = AABB, 2 = ABAB, 3 = ABBA, 4 = BAAB, 5 = BABA, 6 = BBAA). Baseline characteristics of individuals randomized to each condition will be compared to verify if the randomization was successful. Health professionals referring the participants to the study platform are not aware of the randomization sequence, and even if they were, they could not control the participants’ allocation as they could not predict the sequence status at the time of the participants’ access to the study platform. Similarly, the researcher assigning the participants to each arm has no control over the order of enrolment (i.e. over who will access the online platform and when), and differs from the researcher performing the statistical analysis at a subsequent stage. The data analyst will be blinded to the intervention assigned to the participants. The study is single-blinded: participants are not unaware of the intervention received as they are active parts of the intervention. Data collection at baseline and outcome assessments are carried out in a computerized manner via study platform and resorting to self-administered instruments, thus the researcher has no influence over the measurements.

### Variables and data collection methods

Data collection will be carried out at three different time points: i. at baseline (*t*_0_); ii. post-intervention (3 months after baseline; *t*_1_); and iii. follow-up (6 months after baseline; *t*_2_). Table 1 presents the schedule of interventions and assessments. Primary and secondary outcomes are measured through self-report instruments composing the data collection protocol. All data will be collected in a computerized manner through the study online platform. Three and six months after the baseline (*t*_1_ and *t*_2_), the participants are invited by email to fill in the online questionnaires and, as an attempt to avoid missing data, two reminders are foreseen for each assessment (see Fig. 1).

#### Intervention vs. control condition

The independent variable/factor is a dichotomous variable describing the intervention with iSupport or a control with a minimal education-only intervention (e-book).

##### Comparison condition: education-only

The control group will receive a minimal education-only intervention, consisting on an e-book created by the European Commission and Alzheimer Europe [53], and translated to European-Portuguese by the Association Alzheimer Portugal [54]. The manual contains information on relevant topics for dementia and caregiving, including basic information about dementia; practical tips on managing dementia; the changing needs of a person with dementia; dealing with care provision and with the death of the care receiver; caring for oneself and finding emotional support; relevant legislation (e.g. advance directives); and how to get help and reach the national Alzheimer’s Association. In Portugal there is no standard care in what concerns support to IC of PwD; besides sporadic face-to-face training and support initiatives, the most common support given to IC of PwD is in the form of informative material (e.g. leaflets, books, online resources) provided by health and social work professionals. The e-book selected is among the most complete resources for IC of PwD available in Portugal. Together with access to the e-book, the participants allocated to the control group will receive weekly reminders to read the manual, as a measure to avoid bias due to different follow-up (as reminders are provided to the intervention group).

#### Outcomes

The outcomes of this study have been widely used in intervention studies assessing the effectiveness of internet-based support tools [27]. The primary outcome is caregiver burden measured with the Zarit Burden Interview (ZBI), Portuguese validated version [48, 49], total score, at *t*_1_. The instrument comprises 22 items answered on a 5-point scale, ranging from 0 (never) to 4 (almost always) except for the final question on global burden, rated from 0 (not at all) to 4 (extremely). Total score for the ZBI ranges from 0 to 88 points, with higher scores indicating greater burden. The ZBI has good internal consistency (e.g. α = 0.89 in [55]), test-retest and interrater reliability as well as construct and concurrent validity, including reports of positive correlation with depression symptoms and time devoted to care provision [56, 57]. Regarding the psychometric properties of ZBI in Portugal, face, content, ecological, discriminant and convergent validity were documented, along with test-retest reliability (ICC = 0.93, CI95% 0.88–0.96, *p* < 0.001) and internal consistency (*α* = 0.88) [57]. The ZBI is one of the most used instruments to measure burden in intervention studies with caregivers [18].

The following variables are included as secondary outcomes: (i) symptoms of depression and anxiety measured through the Portuguese version of the Hospital Anxiety and Depression Scale (HADS) [50, 51], total scores. The instrument comprises two subscales with 7 items each, using a 4-point scale. Total scores for each scale range from 0 to 21, with higher scores indicating more severe anxiety or depression symptoms; (ii) quality of life measured by the Portuguese version of the WHOQOL-BREF physical, psychological, social relationships and environment [58, 59], total transformed scores. The instrument contains 26 items, for total transformed scores ranging between 0 to 100 points, with higher scores denoting higher quality of life; (iii) positive role appraisals mediating between the stressor and caregiver well-being, measured through the Portuguese version of Positive Aspects of Caregiving (PAC) [57, 60], total score. This instrument comprises 11 items answered in a 5-point scale, for a total score ranging between 11 to 55 points and higher scores representing more positive appraisals; and (iv) general self-efficacy, measured through the total score of the Generalized Self-efficacy Scale [61, 62]. The scale comprises 10 items answered in a 4-point scale for a total score ranging between 10 to 40 points, and higher scores representing a higher general self-efficacy. The instruments used for data collection can be found in the references provided or under request to the authors of each instrument. The variables defined as primary and secondary outcomes are assessed at baseline and repeated measurements are performed at *t*_1_ and *t*_2_. An attempt to reach participants from both groups who do not complete the assessments will be made in order to collect the reasons.

#### Covariates

Variables measured at baseline (*t*_0_) include sociodemographic characteristics of IC, namely their age, gender, marital and occupational status, years spent in education and residence area. In addition, a questionnaire for caregiving characterization collects information on the type of care provided, i.e. paid/non-paid (screening); duration (number of years providing care) and frequency of care provision (number of hours per week); existence/non-existence of other care providers; relationship with the care receiver; and cohabitation/non-cohabitation with the care receiver. Moreover, age and gender of the care receiver are collected, as well as information on the care receiver’s living arrangements (living in the community vs. institutional care; screening), on the degree of care receiver’s dependence (as subjectively evaluated by the IC); and on the duration of dementia symptoms (as perceived by the IC). ICT usage is characterized by the frequency of internet use.

### Sample size calculation

As a baseline for estimating the sample size, the primary null hypothesis was stated:*H0: The change in mean caregiver burden from baseline at t*_1_
*is the same in informal caregivers of people with dementia assigned to the iSupport program as in those assigned to a minimal education-only intervention.*

A two-sided alternative hypothesis was assumed:*H1: The change in mean caregiver burden from baseline at t*_1_
*is different in informal caregivers of people with dementia assigned to the iSupport program as in those assigned to a minimal education-only intervention.*

Caregiver burden at *t*_1_ (measured with the ZBI) is the primary outcome measure, therefore used for the sample size calculation. The effect size was defined taking into account a meta-analysis reporting a mean standardized effect size of 0.65 (95% confidence interval [0.46–0.84]), for multicomponent interventions, on caregiver burden [18]. Assuming a smaller but still moderate standardized effect size of 0.5 (E/S), equivalent to about a 6-point endpoint mean difference, and a SD of 12 based on Bachner and Rourke [63] and assuming an *α* (two-sided) = 0.05 and a β = 0.2, a sample size of 64 per group was calculated as follows:

*Standardized effect size (E/S) = 6 ÷ 12 = 0.5.*

16 ÷ (standardized effect size)^2^ = 16 ÷ 0.25 = 64

Conservatively allowing for a larger dropout rate of 30% found in the literature for these interventions [47], a total of 92 informal caregivers per group was calculated:

16 ÷ 0.25 × 1.43 = 92

With a sample size of 92 per group and a dropout rate no larger than 30%, the study will be able to detect an intervention effect of 0.5 for the primary outcome.

### Statistical analysis

Descriptive statistics will be used to characterize the IC enrolled in the intervention study: means and standard deviations for the continuous variables presenting normal distribution; medians and percentiles for continuous variables not normally distributed or ordinal variables; frequencies for nominal variables. At *t*_0_, the randomization success will be examined by comparing the characteristics of participants in both arms with the adequate statistical methods. Since the outcomes are continuous variables the best measure is the change in the outcome over the course of the study: this approach usually minimizes the outcome variability between participants and offers more power than just comparing values at the end of the study. To evaluate differences between the outcomes of each group, paired t-tests will be conducted and estimates of effect sizes calculated. All *p* values are two-sided with a significance level of 0.05. Multiple regression analyses can be used to correct for possible confounders. Generalized estimated equations (GEE) analysis can be used to examine the maintenance of the intervention effectiveness. The data will be analyzed by a researcher blinded to the group assignment.

The data analysis will follow an Intention-to-treat (ITT) protocol, therefore participants will be analyzed as randomized. This approach is an important protection against bias by preserving the randomization benefits, in particular by balancing known and unknown factors and eliminating selection bias. As the ITT approach requires either no attrition or a strategy to handle missing data, to minimize the first, reminders for both assessments (*t*_1_ and *t*_2_) are foreseen and to address the second, missing data on follow-up measurements will be imputed using multiple imputations. In addition, a per protocol sensitivity analysis will be conducted to ‘bracket’ the likely effects under different conditions. For this purpose, a minimum number of completed lessons (*n* = 5), in addition to the completion of the assessments (*t*_1_ and *t*_2_), will be considered. An interim analysis is foreseen, to be implemented before the participants’ enrolment is completed. As the intervention study does not raise relevant concerns about intervention safety, a single look/interim assessment, when half of the sample is reached, is planned. Elements to monitor in the interim analysis include recruitment, adherence to intervention, follow-up completeness, and reported harms. Measures that might arise from the interim analysis include extending the study in time, increasing the study sample or stopping the study. The study should be stopped in case of determination of benefit or harm, or in case of being identified a negligible chance of demonstrating effectiveness if the intended number of participants were fully enrolled. Only the research team will have access to the interim results and make the final decision to terminate the trial if fulfilled the stopping criteria. To minimize type I error, the *α* will be decreased in the interim analysis. All analyses will be conducted using SPSS for Windows.

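### Baseline comparisons are a poor check on randomisation, and an unadjusted test of change with optional regression gives up precision that a prespecified baseline-adjusted analysis would keep

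*Protocol article*

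**What the plan says.** The protocol article states twice that baseline data will be used to judge the randomisation. Randomization and blinding says: "Baseline characteristics of individuals randomized to each condition will be compared to verify if the randomization was successful". Statistical analysis says that at baseline "the randomization success will be examined by comparing the characteristics of participants in both arms with the adequate statistical methods". The methods are not named, but the same section sets one rule for all testing: "All *p* values are two-sided with a significance level of 0.05".

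For the outcomes, Statistical analysis prefers change over the study to the end value, and continues: "To evaluate differences between the outcomes of each group, paired t-tests will be conducted and estimates of effect sizes calculated". Adjustment appears only as a possibility: "Multiple regression analyses can be used to correct for possible confounders". That section names no covariates and gives no condition for adjusting.

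The Covariates section lists many baseline variables ("Variables measured at baseline (*t*_0_) include sociodemographic characteristics of IC, namely their age, gender, marital and occupational status, years spent in education and residence area", followed by caregiving, care-receiver and internet-use items) but ties none of them to a model. Baseline values of every outcome will be available: "The variables defined as primary and secondary outcomes are assessed at baseline". Allocation is by permuted blocks: "Blocks of four with equal number of As (intervention) and Bs (control) will be used". No stratification factors are stated.

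**The concern.** Two things are weak here.

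First, when permuted blocks are applied properly, the null hypothesis of a baseline comparison is true by design. A small p-value is then a chance event, and reading it as a sign of unsuccessful randomisation is a mistake. With this many variables, such p-values will be common.

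Second, baseline information enters the main analysis only through the change score. Any further adjustment is optional, and its target is described only as possible confounding. In a randomised comparison, a baseline confounder is a chance imbalance, so the wording leaves room to choose covariates because they look unbalanced rather than because they predict burden. That choice recovers little precision.

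Precision matters in this trial. The Discussion concedes that burden is hard to shift, that effects may be smaller when measured with the ZBI, and that recruitment carries most of the study's risks.

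**Working it through.** **1. The plan's own figure.** The inputs are in Sample size calculation: difference 6, SD 12, two-sided α 0.05, power 0.80, dropout 30%.
- The plan's rule gives 16 ÷ 0.25 = 64 per arm. The exact two-sample t calculation gives 63.8, so 64 is reproduced.
- For dropout, 64 ÷ 0.7 = 91.4, so 92 per arm. The plan's 64 × 1.43 = 91.5 agrees.

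**2. How often chance alone gives a significant baseline difference.** My count of non-screening variables in the Covariates section is 6 sociodemographic + 5 caregiving + 4 care-receiver + 1 internet use = 16. The Outcomes section adds 9 baseline scores (ZBI, two HADS subscales, four WHOQOL-BREF domains, PAC, self-efficacy), for 25 in all. If tests are independent and randomisation is perfect:
- 16 tests: 1 − 0.95^16 = 0.56, with 16 × 0.05 = 0.8 expected.
- 25 tests: 1 − 0.95^25 = 0.72, with 25 × 0.05 = 1.25 expected.

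Correlation among the variables lowers both probabilities, but not the expected counts.

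**3. Precision of the change score against ANCOVA.** Assumptions: SD 12 for the ZBI score at both times, 64 evaluable per arm, and a baseline-to-3-month correlation r of 0.5 or 0.7. The protocol gives no value for r.
- SD of change = 12 × √(2(1 − r)).
- Residual SD after ANCOVA = 12 × √(1 − r²).
- The ratio of the two variances is (1 + r)/2.
- Power ≈ Φ(6 ÷ (SD × √(2/64)) − 1.96).

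| r | Analysis | SD | 6 ÷ SE | Power, formula | Power, simulation |
|---|---|---|---|---|---|
| 0.5 | change | 12.00 | 2.83 | 0.81 | 0.81 |
| 0.5 | ANCOVA | 10.39 | 3.27 | 0.90 | 0.91 |
| 0.7 | change | 9.30 | 3.65 | 0.95 | 0.95 |
| 0.7 | ANCOVA | 8.57 | 3.96 | 0.98 | 0.97 |

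The simulation added 16 independent covariates, four of them weakly prognostic. If the 12 points were instead the SD of change, the change score would have power 0.81 at either r. ANCOVA would then have 0.90 at r = 0.5 and 0.87 at r = 0.7 (residual SD 12 × √0.85 = 11.06; 6 ÷ SE = 3.07).

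**4. Adjusting only for variables found unbalanced (same simulation).** Covariates with baseline p < 0.05 were added to the change-score model.
- Power was 0.82 at r = 0.5 and 0.95 at r = 0.7, almost the same as with no adjustment.
- Type I error was 0.041 and 0.039, slightly conservative.
- Taking the smallest p-value among the unadjusted, imbalance-adjusted, ANCOVA and fully adjusted analyses raised type I error to 0.102 and 0.094.

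**The case against.** Several stronger readings are tempting, and the document does not support them.

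- *The adjusted model will be picked from chance imbalances.* Nothing links the baseline comparison to covariate choice. The two statements are separated by other material, and regression is only optional. Selection from imbalance is something the wording permits, not something it plans.
- *There are two competing primary answers.* Sample size calculation states the primary hypothesis as change in mean burden at 3 months, and the t-tests are definite where regression is not. The plain reading is an unadjusted main analysis with supplementary regression. The label of those t-tests as paired is a separate matter; I take them as a test of change between arms because the hypothesis is one.
- *Type I error is inflated.* A strict test-then-adjust rule does not inflate it. The figure near 0.10 needs a free choice among four results, which the protocol does not describe.
- *Baseline ZBI drops out when it is balanced.* It does not, because the change score always uses it. The loss is one of efficiency.
- *A baseline comparison can never reveal a fault.* This is too absolute. Sampling and recruitment says that a researcher applies the randomisation key, so a gross imbalance could point to an implementation error. Checking allocations against the sequence tests that directly.
- *A failed check is the expected result.* The protocol sets no criterion for failure. The 56% to 72% also assumes independent significance tests, and the protocol itself reports that ZBI correlates with depression symptoms and care time.

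All of that stands. It is also fair that the covariate list of a supplementary regression may be left to an analysis plan, and that blinding the analyst limits steering towards one arm. It does not limit selection among p-values. What remains does not depend on missing detail: the document states a poor purpose for the baseline comparison, and names a main analysis that uses a variable already in hand less efficiently than it could.

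**Conclusion.** The point holds in a limited form. Baseline comparison is a poor check of randomisation, and nominal differences are likely by chance (56% to 72% under independence, lower with correlation). The more useful finding is the precision lost by an unadjusted change score. At 64 per arm and effect 0.5, ANCOVA on baseline ZBI raises power by about 10 percentage points at an assumed correlation of 0.5 and by about 2 at 0.7. That gap comes from the choice of change score over ANCOVA, not from the baseline comparison, and its size depends on a correlation and an SD interpretation that the protocol does not settle. A reader might infer a biased or error-inflating analysis; the text and the calculations do not show one. The stated sample size is unaffected.

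**What to change.** In both sections, replace the check of randomisation success with a descriptive table of baseline characteristics by arm, without tests. If implementation is in doubt, compare the allocation log with the generated sequence.

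State the primary analysis as a between-group comparison of ZBI at 3 months adjusted for baseline ZBI, included whatever balance is observed. The same model can be fitted within the multiple imputation already planned. Label any other adjusted model exploratory.

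The cost is a change of wording. Baseline ZBI is already collected, and recruitment stays at 92 per arm.
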